### Concealment mechanism {16b}

PHCs will be identified, and permission given to participate before allocation. After the central allocation of all clusters has been performed, each PHC will be notified of their allocation by the project manager. Given the pragmatic nature of this care-delivery trial, individual participants can only be recruited after allocation, and there will be no concealment before recruitment.

## Assignment of interventions: blinding

### Who will be blinded {17a}

Owing to the pragmatic nature of the trial, participants, care providers and outcome assessors will not be blinded to the allocation group. Data analysts, the Principal Investigator and the Steering Committee will remain blinded until the end of the study and database lock when the primary analysis will be performed.

### Procedure for unblinding if needed {17b}

All members of the clinical care team will remain unblinded throughout the study. As the statistician, Principal Investigator and Steering Committee are not directly involved in patient care in this study; there are no foreseeable reasons why the study would need to be unblinded.

## Data collection and management

### Plans for assessment and collection of outcomes {18a}

Independent, GCP-certified, trained, study team members will be involved in data collection at each stage. Data collection will occur on three occasions at both the intervention and control sites: baseline (after 12 weeks’ gestation), 9–12 weeks and then 9–12 months post-birth. All data will be captured on tablet computers using the SMARTHhealth app adapted for the clinical research forms (CRFs). Data will be de-identified, saved and stored on a secure server at the George Institute of Global Health, India. Strategies to ensure data quality include using published, validated questionnaires and the CRFs developed and user tested in the SMART Health Pregnancy pilot study. The field team supervisor will check approximately 10% of all CRFs for accuracy against source data or by direct interview with participants.

### Plans to promote participant retention and complete follow-up {18b}

Community education events will be held at intervention and control sites to promote the study and awareness of women’s health, anaemia, cardiovascular disease and diabetes. Refreshments and transportation costs will be provided to women at the baseline and annual study assessments.

ASHAs and PCPs will receive a small payment per participant to compensate for the time spent on the study. For women who move away from the study sites during their follow-up period, information on pregnancy complications and outcomes will be collected by phone where possible.

### Data management {19}

Data management will be performed in line with the study Data Management Plan. All baseline and outcome data will be entered digitally into the SMARThealth Pregnancy researcher platform. Access to data will be restricted to delegated study staff only and will require multifactor identification with a digital log kept of all logins. The trial manager and data managers will be primarily responsible for data quality. The trial manager will work with the project managers at both sites to ensure data quality, including completeness of data, data validation, data query management and training of database users. Monthly audits will be conducted to ensure the completion and quality of data captured.

### Confidentiality {27}

Throughout the study, all efforts will be made to maintain participant confidentiality. Each subject enrolled in the project will have a unique identifier (ID) of six digits. The first digits denote the study state (00 = Telangana, 01 = Haryana). The final four digits will denote the participant’s unique number, e.g. 00–0001 will be in Telangana and will be the first participant screened for both sites; 01–0002 will be in Haryana and will be the second participant screened for both sites. Participants who are screened but do not give consent or withdraw from the study will also receive a study ID to calculate intervention reach. Tablet computers used for data collection as part of the intervention and for the study assessments will be password protected with multifactor authentication. They will be used only by authorised users and stored in a secure location when not in use. Local data stored on mobile devices will be deleted daily following online database synchronisation. Participant-identifiable data will be collected in a separate database to the research data set and linked using a unique identifier (see above for details). This information will be held only for the study duration to enable follow-up by the study team.

### Plans for collection, laboratory evaluation and storage of biological specimens for genetic or molecular analysis in this trial/future use {33}

No biological samples will be collected or stored. Haemoglobin will be estimated using validated point-of-care devices. For the small number of women who develop GDM and require endline HbA1c, private local laboratories will process the samples with no sample storage.

## Statistical methods

### Statistical methods for primary and secondary outcomes {20a}

The primary analysis will be by intention to treat conducted at the participant level, using either random-effects models or generalised estimating equations adjusted for PHC clustering. We used a matched-pair design to balance cluster characteristics prior to randomisation, as recommended for community-based trials with a limited number of clusters [40]. Given the relatively small number of clusters, the analysis will not adjust for matching since this has been shown to provide unbiased estimates of the randomised intervention effect [41] and provide similar power to a matched analysis [40]. An unmatched analysis has the advantage that it can easily be conducted using participant-level data whilst allowing estimation of the intra-class correlation coefficient.

The final analysis is anticipated to occur 36 months after recruitment of the first participant. For the groups to be declared significantly different, the *P* value for the primary outcome must be ≤ 0.05. We will report the point estimate and confidence interval and present an assessment of the clinical relevance of our findings.

Baseline data will be presented for both groups. Continuous variables will be assessed for distribution, with appropriate statistical transformation (e.g. log or cubic splines) to correct for non-normality. Subgroup analyses will be performed by study location (Telangana or Haryana) to explore the effects of contextual factors on outcomes of interest. A detailed statistical analysis plan will be developed and publicly available before unblinding.

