## Trial design {8}

A pragmatic, type 2 hybrid effectiveness/implementation, parallel-group cluster randomised superiority trial in two states in India (Haryana and Telangana). Thirty PHCs in Telangana and Haryana will be randomised 1:1 using a matched-pair design accounting for cluster size and distance from the regional centre. As the intervention is aimed at health workers working as teams (community health workers and PHC doctors), effectiveness is best evaluated through a cluster randomised trial with clustering at the PHC level (Fig. 1).

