*Follow-up after anaemia, GDM or HDP condition*: We will compare how many women with anaemia undergo a haemogloblin test; how many women after HDP or GDM undergo BP measurement, and how many women after GDM undergo a glucose assessment (fasting or random capillary glucose, OGTT or HbA1c) within 6 weeks and 6 months and 12 months after birth.(4)Women’s wellbeing, mental health, lactation practice
*Wellbeing*: The impact of the intervention on women’s general wellbeing, mental health. We will use locally validated mental health and wellbeing tools (EQ-5D-3L, PHQ9 and GAD7 [35]) to compare changes between baseline and at 12 months.
*Lactation*: is one of the few interventions for which evidence supports a positive impact on maternal and newborn long-term health following a high-risk pregnancy, specifically one affected by GDM [36]. We will assess whether the additional support provided through the intervention can improve lactation practice using WHO Infant and Young Child Feeding indicators [37].

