### Participant timeline {13}

PHCs will be recruited and randomised before individual participant recruitment commences. After randomisation, ASHAs in the intervention clusters will attend the education programme to receive training on the clinical conditions, use of the point-of-care devices and SMARThealth Pregnancy app. Individual participants will be approached by their ASHA worker to participate after 12 weeks’ gestation. If they consent to participate in the study, a study team member will complete a baseline assessment, which includes questionnaires, blood pressure and haemoglobin measurement. A study team member will perform a mid-point assessment between 9 and 12 weeks after birth to capture events and healthcare utilisation including out-of-pocket costs around the time of birth. A study team member will conduct the final study visit 9–12 months after delivery, which will involve completing questionnaires, and measuring haemoglobin and blood pressure (Table 2).

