#### Intracluster correlation

The nature of the intervention as a health system intervention precludes individual randomisation. Estimating intracluster correlation coefficients (ICCs) was based on the SMARThealth Pregnancy pilot study extrapolations [38]. Across the four sites in the pilot study, the ICC for anaemia was 0.019; thus, an ICC of 0.02 has been assumed for the study.

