#### Variability in the primary outcome and estimated effect size

The pilot study’s prevalence of anaemia during pregnancy was higher than the reported national levels, likely due to selection differences and differences in testing techniques (venous sample vs POC device used in the pilot study).

The prevalence of anaemia is slightly higher in non-pregnant than pregnant women (national estimate for India 53 and 50% respectively, NFHS 5 [39]). The national target for anaemia reduction is three percentage points per year as part of the Anaemia Mukt Bharat programme [18].

We estimate that our intervention will improve anaemia rates in these populations by 9% over 3 years (i.e. 53 to 44%). Determining a minimally clinically important threshold for anaemia is challenging. We selected the target decrease in anaemia as it was in keeping with the AMB programme [18], and to be an achievable and programmatically meaningful target with optimal support for anaemia prevention. Whilst anaemia is anticipated to decrease in the population because of the ongoing government programmes (including AMB), evidence from our pilot study is that compliance and implementation issues exist on the ground. Our intervention was designed to enhance delivery of the government programme and reaching of national anaemia reduction targets.

Given 30 clusters and an ICC of 0.02, 86 women per cluster are needed to detect a 9% absolute reduction (53 to 44%) with 80% power (a total sample size of 2580). Allowing for losses to follow-up of 20%, a sample size of 108 women per cluster is needed (a total sample size of 3240).

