## Assignment of interventions: allocation

### Sequence generation {16a}

Before randomisation, each PHC will be paired with another similar PHC from the same state and with similar characteristics. The pairing will be based on:

State (Telangana or Haryana)Distance in km to the district headquartersPHC total population sizeLocal advice on population similarity (socio-economic, demographic, etc.).

Within each PHC pair, one PHC will be randomly allocated to intervention using a computer-generated randomisation programme. The other PHC will then be designated as the control. To ensure a 1:1 balance (the same number of PHCs allocated to intervention and to control) within each state, we will select an even number of PHCs in each state. Sixteen PHCs will be enrolled from Telangana and 14 from Haryana.

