Our study will be conducted in two states with very different socio-cultural environments, which will improve the generalisability of our findings to other states in India. We are conducting this study as a hybrid effectiveness-implementation design. A separate protocol will be published on the planned implementation outcomes that we will capture through a detailed process evaluation. The analysis of implementation outcomes and strategies will inform the iterative development and steps needed for the eventual scale-up and adoption of the intervention more widely; alternatively, it will explain the factors that contributed to a null trial. As part of the process analysis, we will continue refining our logic model and assumptions regarding how the intervention works and the barriers to implementation, as well as the economic benefits and implications.

We acknowledge our study design has limitations. Owing to funding constraints, we can only involve community health workers from two villages affiliated with each PHC. Thus, the intervention will not be at the population level which might affect primary care physician engagement. We will explore this in detail in our process analysis. The nature of the trial design means there could be benefits above usual care in the control clusters. Participants in both study arms will have their haemoglobin tested and their blood pressure measured at the study visits. Ideally, after a high-risk pregnancy condition, follow-up would extend for life, which is clearly impractical and prohibitively expensive in the context of this study. We believe demonstrating engagement beyond 6 weeks after birth will be a strength. The nature of the complex intervention means that blinding of participants is not practical or feasible, increasing the likelihood of information bias. To minimise this, we will ensure that the trial statistician and investigator group remain blinded to allocation until the primary analysis has been performed.

Given the longitudinal nature of recruitment, not all potential participants will be pregnant before the study starts; therefore, randomisation must occur before participants are recruited. This could bias recruitment, as community health workers will know their allocation group when approaching pregnant women. However, in our pilot study, this was not the case: we achieved equal recruitment and retention rates across both groups.

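### The primary model leaves out state and the other pairing factors as covariates, which makes the test conservative if they matter; baseline haemoglobin should be pre-specified alongside them

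*Protocol article*

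**What the plan says.** **Pairing.** Sequence generation {16a} states that before randomisation "each PHC will be paired with another similar PHC from the same state and with similar characteristics". Pairs are formed on state, distance to district headquarters, PHC population and local advice, and one PHC of each pair is randomised to intervention. Telangana contributes 16 PHCs and Haryana 14, so there are 8 and 7 pairs.

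**Primary model.** Statistical methods {20a} gives a random-effects model or GEE, with PHC clustering as the only adjustment named. On matching it says: "Given the relatively small number of clusters, the analysis will not adjust for matching since this has been shown to provide unbiased estimates". It adds that an unmatched analysis has similar power, can use participant-level data and allows the ICC to be estimated. State appears in that section only as a subgroup. Baseline data are to be presented by group, and further detail is left to a later SAP.

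**Baseline and recruitment.** Under Participant timeline {13}, "a study team member will complete a baseline assessment, which includes questionnaires, blood pressure and haemoglobin measurement". Concealment mechanism {16b} says women are recruited after allocation without concealment, and the Discussion concedes: "This could bias recruitment, as community health workers will know their allocation group when approaching pregnant women".

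**Wellbeing.** Under Secondary outcomes, EQ-5D-3L, PHQ9 and GAD7 are used "to compare changes between baseline and at 12 months". No model is named.

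**The concern.** The design takes state, distance and population out of the comparison between arms, and the analysis then puts them back into the error term. The protocol's small-number-of-clusters reason is an argument about 15 pair terms. It says nothing against one degree of freedom for state, or three for state, distance and population. Both of its other practical aims, a participant-level model and an ICC estimate, survive the addition of covariates.

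The unbiasedness argument concerns randomised clusters. It does not reach the women, who enter after allocation through health workers who know their arm and may enrol at any gestation from 12 weeks. The Discussion answers with equal recruitment and retention rates in the pilot, but equal rates do not show equal haemoglobin or gestation at entry.

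At stake are the width of the primary interval, some power, and the credibility of any covariate adjustment chosen after the data are seen.

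**Working it through.** **Inputs from the protocol.** Sample size {14}: "86 women per cluster are needed to detect a 9% absolute reduction (53 to 44%) with 80% power (a total sample size of 2580", and "the ICC for anaemia was 0.019; thus, an ICC of 0.02 has been assumed for the study". There are 30 PHCs, so 15 per arm. Alpha is 0.05, taken as two-sided.

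**Step 1: reproduce the plan's figure.**
- Design effect = 1 + (86 - 1) × 0.02 = 2.70.
- Effective n per arm = 15 × 86 / 2.70 = 477.8. Normal-approximation power with pooled variance is 79.6%, in line with the stated 80%.
- Solving for cluster size with unpooled variance: n = 480.1 per arm, and m = 480.1 × 0.98 / (15 - 480.1 × 0.02) = 87.2, close to 86.
- SE = √[(0.53 × 0.47 + 0.44 × 0.56) × 2.70 / 1290] = √(0.4955 × 2.70 / 1290) = 0.0322. With a t reference on 28 df, power is 77.0%.

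The planned size assumes no gain from covariates or matching.

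**Step 2: where cluster-level covariates act.** Relative to individual variance, a cluster mean has between-PHC variance 0.02 and within-PHC variance 0.98 / 86 = 0.0114. The between-PHC share is 0.02 / 0.0314 = 64%.

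**Step 3: effect of leaving the pairing factors out.** Let f be the share of between-PHC variance that they explain (assumed). Because pairing balances them between arms, the true SE of the arm difference falls to √[(0.4955 / 15) × (0.02(1 - f) + 0.0114)]. The unadjusted model still estimates an SE of about 0.032. Unadjusted results are from cluster-level simulation (8 + 7 pairs, unmatched t-test on 28 df). Adjusted power is from the noncentral t.

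| f (assumed) | True SE | Type I error, unadjusted | Power, unadjusted | Power, adjusted for state (27 df) | Power, adjusted, 3 df spent (25 df) |
|---|---|---|---|---|---|
| 0 | 0.0322 | 5.0% | 77% | 76.9% | 76.6% |
| 25% | 0.0295 | 3.2% | 78% | 83.6% | 83.4% |
| 50% | 0.0266 | 1.8% | 80-81% | 90.4% | 90.2% |

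The adjusted columns take the fitted covariates to carry the whole share f. A hand check on type I error agrees: the null rejection rate is about 2[1 - Φ(1.96 × 0.0322 / true SE)]. That is 2[1 - Φ(2.14)] = 3.2% at 25% and 2[1 - Φ(2.37)] = 1.8% at 50%. The unadjusted intervals are then wider than needed by 0.0322 / 0.0295 = 1.09 and 0.0322 / 0.0266 = 1.21. Simulated bias is about zero throughout.

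**Step 4: baseline haemoglobin.** A between-arm difference of d SD shifts the unadjusted risk difference by about r × d × 0.5, where r is the correlation of baseline haemoglobin with endline anaemia. For an illustrative d = 0.1 this is 1.0, 1.5 or 2.5 points at r = 0.2, 0.3 or 0.5, against a 9-point target. Neither d nor r is in the documents.

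**Step 5: change score against baseline adjustment.** The variance ratio is 2(1 - r) / (1 - r²) = 2 / (1 + r), with r now the baseline-to-endline correlation of the score. It is 1.54 at r = 0.3 and 1.33 at r = 0.5 (assumed), and never below 1.

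**The case against.** The strongest reply is that the protocol made a reasoned choice and that the choice is valid. Pairing within state balances state by design, so omitting it causes no bias; the test errs on the safe side; and the 86 per cluster reproduces without any adjustment. All of that stands. A reader might infer that the trial is underpowered against its own plan, or that ignoring the pairs is an error. Neither follows. If the pairs explain nothing, a paired analysis would have less power (73% against 77%).

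It can also be said that covariate lists belong in the SAP. For baseline haemoglobin this largely stands: the protocol is silent on it, so to read it as excluded goes too far. Likewise, comparing changes in wellbeing does not rule out a baseline-adjusted model. On these two items the point is a request to pre-specify. On the pairing factors the protocol is not silent: it states that matching will not be adjusted for and names clustering as the only adjustment.

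The size of any gain rests on an assumed variance share, and the documents do not say whether the pilot ICC already includes between-state variation. It would also overstate the gain to set 77% against 84-90%, because effective pairing already lifts the unadjusted test to about 78-81%.

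Finally, a reader might infer that covariates would remove recruitment bias. They correct only imbalance in what is measured, and this baseline is taken after cluster allocation.

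**Conclusion.** The point holds as a worthwhile improvement in efficiency and pre-specification. It does not show the planned analysis to be invalid. The stated reasons justify omitting the pair terms but not omitting state, distance and PHC population as covariates. If these explain 25-50% of between-PHC variance, adjustment gains roughly 5 to 10 points of power over the planned test and brings the type I error back from about 3.2-1.8% to 5%. If they explain none, the loss is about 0.1 point for state alone and 0.4 point for all three. The share is an assumption, although the Discussion's own description of the two states as socio-culturally very different makes it unsafe to suppose that it is nil. Baseline haemoglobin deserves a place because recruitment is open and the measurement already exists. How much imbalance it would correct cannot be known from the documents.

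**What to change.** Keep the unmatched participant-level model. In the SAP, before unblinding, pre-specify:
- fixed effects for state, plus PHC population and distance;
- individual baseline haemoglobin and gestational age at baseline;
- the adjusted risk difference as the primary result and the unadjusted one as sensitivity;
- PHQ9, GAD7, EQ-5D and continuous haemoglobin analysed as the endline value adjusted for baseline, in place of a change score;
- a rule for the few missing baselines.

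The cost is SAP wording and up to three cluster-level degrees of freedom (28 to 25). No new data are needed. The SAP should also state that the baseline is measured after cluster allocation and that adjustment addresses measured imbalance only, so the recruitment limitation in the Discussion remains.

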### Outcomes {12}

#### Primary outcome

The primary outcome will be the difference in the proportion of participants with anaemia, defined as haemoglobin measured using a point-of-care test < 12 g/dL at 12 months after delivery between the intervention and EUC clusters. Anaemia has been chosen as the primary outcome as it is the most common condition affecting women during pregnancy and breastfeeding across India. Measurement using a point-of-care device was chosen as this has been recommended in national guidelines and is a common method for diagnosing anaemia in rural settings, thereby reflecting real-world practice. The measurement will be performed by a member of the study team.

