*Implementation*: Fidelity to the intervention protocol for the trial and for the intervention itself and any adaptations during the trial. This will be measured assessing data completeness, and through qualitative methods with health workers.
*Maintenance*: We will explore the system-level factors needed for institutionalisation of the intervention and level of intent to continue to programme in the study settings and more widely using key stakeholder interviews and focus group discussions, as well as policy discourse analysis around maternal health and digital health policy.

(2)Clinical endpoints
*Anaemia*: Haemoglobin will be compared between intervention and EUC clusters as a continuous variable (measured in grams per decilitre on point-of-care test) and as categories of anaemia using the WHO thresholds used for non-pregnant adults: no anaemia > 12.0 g/dL; mild anaemia 11.0–11.9 g/dL; moderate anaemia 8.0–10.9 g/dL; severe anaemia < 8 g/dL
*Diabetes*: Between the intervention and EUC, we will compare venous blood glucose following a 2-h, 75-g oral glucose challenge at 1 year after birth in participants diagnosed with GDM during pregnancy. Blood glucose will be assessed as a continuous measure (in milligrams per decilitre) and as categories of glucose impairment: Normal: < 140 mg/dl, impaired glucose tolerance (IGT): 140–199mg/dl, Diabetes: ≥ 200 mg/dl
*Hypertension*: Blood pressure (BP) will be compared between women who developed HDP. BP will be assessed as a continuous measure (systolic, diastolic and mean arterial pressure) in millimetres of mercury (mmHg) using a validated sphygmomanometer and as a binary category of hypertension (yes/no) defined as BP > 140/90 mmHg(3)Clinical service delivery indicators
*Quality-of-care score*: We will measure differences between the intervention and EUC clusters using a quality-of-care score we have developed specifically for this study. The score comprises an equally weighted composite of clinical outcomes (anaemia, diabetes, hypertension) with measures of access and health professional visit frequency during pregnancy and in the first 12 months after delivery.

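### Cubic splines are named as a cure for non-normality, which they are not, and the same sentence lets the data choose the scale of continuous secondary outcomes

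*Protocol article*

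**What the plan says.** In the protocol article, the section Statistical methods for primary and secondary outcomes {20a} states: "Continuous variables will be assessed for distribution, with appropriate statistical transformation (e.g. log or cubic splines) to correct for non-normality". The sentence follows one about presenting baseline data by group, but it limits itself to no set of variables. The same section adds: "A detailed statistical analysis plan will be developed and publicly available before unblinding".

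The continuous outcomes that the sentence could reach are listed under Secondary outcomes:

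- Clinical endpoints: "Haemoglobin will be compared between intervention and EUC clusters as a continuous variable", in grams per decilitre. Glucose (mg/dL) is compared in women who had gestational diabetes. Systolic, diastolic and mean arterial pressure (mmHg) are compared in women who had a hypertensive disorder of pregnancy.
- Wellbeing: EQ-5D-3L, PHQ9 and GAD7 are to be used "to compare changes between baseline and at 12 months".

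The primary outcome is of another kind: "The primary outcome will be the difference in the proportion of participants with anaemia", a yes/no variable at a haemoglobin threshold of 12 g/dL.

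**The concern.** The sentence gives splines a purpose that they do not serve. A spline expands a covariate into several terms so that its relation to the outcome can bend. The outcome keeps its own distribution. An analysis plan written to agree with this sentence would inherit the mistake.

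Two further weaknesses follow from the same wording. First, the transformation is triggered by what the distribution turns out to look like. The same endpoint could then be reported as a difference in measured units or, after a log, as a ratio of geometric means, and nothing stated in advance says which. Second, the log has no value at zero or below, so it offers no remedy for the change scores planned for the wellbeing scales. Of the two named remedies, then, one does not address non-normality at all and the other is unavailable for the outcomes that are planned as changes.

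**Working it through.** **1. The plan's own figure, to settle whether it is involved.** Inputs from Sample size {14}: 30 clusters, ICC 0.02, 86 women per cluster, 53% against 44%, 80% power, 20% loss. A two-sided 5% level is assumed, because the protocol gives 0.05 without stating sidedness.

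- Design effect = 1 + (86 − 1) × 0.02 = 2.70.
- Effective number per arm = 15 × 86 / 2.70 = 1290 / 2.70 = 477.8.
- Standard error under no difference, with mean proportion 0.485: √(2 × 0.485 × 0.515 / 477.8) = 0.0323. Under the alternative: √((0.53 × 0.47 + 0.44 × 0.56) / 477.8) = 0.0322.
- Power = Φ((0.09 − 1.96 × 0.0323) / 0.0322) = Φ(0.83) ≈ 79.6%, against 80% stated.
- Loss: 86 / 0.8 = 107.5, so 108 per cluster, and 108 × 30 = 3240.

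The stated figures reproduce. They concern a binary outcome, so no distributional transformation enters them.

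**2. Does a spline correct non-normality?** With assumed data, a lognormal outcome was drawn for 2580 women, together with an arm indicator and a normally distributed covariate unrelated to the outcome.

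| Quantity | Skewness |
|---|---|
| Outcome as measured | 6.59 |
| Residuals after arm and a cubic spline of the covariate | 6.58 |
| Log of the outcome | 0.10 |

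The spline leaves the skewness as it was. If a covariate had a strong curved effect, a spline could tidy the residuals by repairing the model for the mean. That is still not a transformation of a non-normal variable.

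**3. Can a log be used on the planned changes?** Write c for 12-month score minus baseline score. If the changes are symmetric about zero, P(c < 0) = P(c > 0), so P(c ≤ 0) = ½ + ½ P(c = 0), which is at least one half. For illustration, PHQ9-like scores from 0 to 27 were drawn independently at the two times from assumed skewed distributions, with follow-up somewhat lower than baseline. About 62% of the changes were zero or negative. The exact share depends on those distributions. That some values fall at or below zero does not.

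**4. Where the log is legitimate.** Haemoglobin, glucose and blood pressure are compared as levels and are strictly positive, so a log is defined for all of them. For these outcomes only the choice of scale is open.

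**5. What baseline adjustment offers.** Take equal variance σ² at both times, correlation ρ between them, and set clustering aside.

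- A change score has variance 2σ²(1 − ρ).
- The baseline-adjusted 12-month score has residual variance σ²(1 − ρ²).
- The ratio of adjusted to change is (1 − ρ²) / (2(1 − ρ)) = (1 + ρ)/2, which is below 1 for every ρ below 1.
- Against an unadjusted 12-month level, the ratio is 1 − ρ², which is below 1 whenever ρ is not zero.

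**6. Which outcomes have a baseline value.** Participant timeline {13} lists questionnaires, blood pressure and haemoglobin at baseline, and no glucose. The content of Table 2 is not visible in the text at hand. The glucose test in pregnancy is a fingerstick capillary sample (Intervention description {11a}), while the endline glucose outcome is venous (Secondary outcomes).

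**The case against.** Much can be said for the protocol.

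- **The wording is loose.** The log and the spline are examples, and the transformation is to be an appropriate one. A log of zero or negative values would not be appropriate. A reader might infer that women with such changes will be dropped, but nothing in the text assigns a log to PHQ9, GAD7 or any change score. Comparing changes can also be done with a baseline-adjusted model. This stands, and it limits the log point to saying that the named remedy is unavailable there.
- **Scope.** The sentence follows one on baseline data and might concern baseline variables or covariates, where splines have a proper use. The section heading and the unrestricted wording point the other way. Even for a baseline variable, correcting non-normality is not what a spline does.
- **Safeguards.** Under Who will be blinded {17a}, analysts stay blinded until database lock, and the analysis plan is to be public before unblinding. A check of distributions can therefore be pooled and blind to arm. This removes most worry about a biased choice of scale. It does not by itself fix the scale in advance.
- **Units.** One might read the outcome list as promising effects in g/dL, mg/dL or mmHg. It gives units of measurement and promises no effect scale.
- **Direction.** One might suppose that women who worsen would be the ones affected. With change taken as 12 months minus baseline, negative PHQ9 and GAD7 values are improvements.
- **Small subgroups.** If 5% to 15% of the 15 × 86 = 1290 women per arm had one of the qualifying conditions, 0.05 × 1290 ≈ 65 to 0.15 × 1290 ≈ 194 would enter the glucose or blood pressure comparison. That prevalence is assumed. The figures count women and measure no error, and they concern outcomes for which a log is defined. They do not size this point.

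**Conclusion.** The point holds as a minor one. The protocol misstates what cubic splines do. This is an error in the text, not a detail left to the analysis plan. The sentence also makes the scale of continuous outcomes depend on the observed distribution, and its other example cannot be applied to the zero and negative changes that the EQ-5D-3L, PHQ9 and GAD7 comparisons will produce.

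No design figure changes, and no bias can be quantified from the document. The consequence is confined to the continuous secondary outcomes. The conclusion on splines rests on what a spline is; the simulated skewness only illustrates it. The conclusion on the log needs only that some women do not change or have a negative change. The reading that the plan will discard or distort these women's data is not supported.

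**What to change.** Before unblinding, in the protocol sentence or in the analysis plan that it promises:

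1. Remove cubic splines as a remedy for non-normality. Keep them only for continuous covariates whose effect may be curved.
2. State the analysis scale of each continuous outcome, with the measured scale as default.
3. Analyse 12-month EQ-5D-3L, PHQ9, GAD7, haemoglobin and blood pressure in the clustered model with the woman's baseline value as covariate, in place of raw or transformed change scores. Report mean differences with confidence intervals, using inference that respects clustering and includes a small-sample correction for 30 clusters.
4. Do not require a baseline covariate for glucose, because no comparable baseline measurement is listed.

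For the five outcomes in item 3, the baseline questionnaires, haemoglobin and blood pressure are already planned, so no new data are needed. The cost is a few sentences and slightly more analysis work. The return is a scale fixed in advance and, under the assumptions of step 5 of the working, some gain in precision.
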